## Trial intervention group: sleep extension and education

2

The aim of the intervention is to increase habitual sleep duration. Following the baseline assessment period, participants randomised into the sleep condition will be provided an individualised sleep extension and education session with an experienced sleep researcher. The sleep extension and education sessions consist of three core elements:(1)Sleep scheduling: This component is based on behavioural principles for sleep scheduling [40]. The researcher will use sleep data collected from actigraphy during the participants' baseline assessment to calculate the participants' average bedtime, wake-up time and habitual nightly sleep duration. Based on these calculated estimates, participant will be 'prescribed’ an extra 20% of time to be spent in bed at home each night across the 3-week intervention period. To facilitate uptake of the intervention into existing sleep/lifestyle routines, participants will be asked to go to bed 15 min earlier each night gradually until their bedtime matches the additional 20% prescribed (this transition may take anywhere between 3 and 7 days). Participants will be asked to maintain this new 'time-in-bed’ for two more weeks. The total intervention period therefore spans 3 weeks (1 week of transitioning to the new sleep schedule, and 2 weeks of maintaining the new schedule). For example, a participant with an average bedtime of 11:30pm, and an average habitual nightly sleep duration of 6.5 h will be prescribed an additional 1.3 h ‘in-bed’ time each night, to be achieved gradually by going to bed 15 min earlier each night until it matches 10:10pm.(2)Sleep Education Online modules: Participants will view 4 × 10-min educational video vignettes (purpose-developed by research team) providing basic education about sleep and sleep health. The topics covered include a) The fundamentals of sleep & circadian functions; b) The benefits of sleep for physical performance, road safety, cognitive and physical functioning; c) The benefits of good sleep for mental health & social functioning and d) The 'SIMPLE’ strategies; Practical tips and tools for supporting healthy sleep. These tips and tools were purpose-developed by the research team and centred on healthy sleep hygiene principles. The SIMPLE strategies include information about sleep 'Scheduling’ and regularity, 'Implementing a pre-bed routine’, 'Minimising screen time’ in the hours before bed, making lifestyle changes aimed at 'Prioritising sleep’, 'Learning to manage stress', and understanding how to make your 'Environment’ conducive to sleep. Participants view the video vignettes at their initial sleep scheduling session and are provided links to the videos via reminder text messages at two other time points in the intervention period (end of Week 1, and 3) encouraging them to revisit this content in their own time.(3)Motivational interviewing and sleep pledge: After viewing the online modules, and receiving their new sleep schedule, the researcher will use motivational interviewing techniques to explore participant's self-efficacy, self-reported sleep needs and/or self-reported barriers to managing sleep health and timing. Using the framework of the 'SIMPLE’ strategies for improving sleep, participants will be provided with their new sleep Schedule, and asked to reflect on which two of the remaining 5 'SIMPLE’ strategies they would be able to commit to and implement for the duration of the intervention period. This process will facilitate autonomy and self-efficacy around sleep scheduling and timing, encouraging maximum fidelity to the intervention sleep schedule. To facilitate participant retention and commitment to the intervention schedule, participants will be asked to sign a 'pledge’ of their commitment to their agreed upon sleep schedule and choice of sleep improvement strategies for the duration of the intervention.

### Placebo group: diet and nutrition education

2.1

The diet and nutrition education was chosen as a comparator (placebo arm) for this trial since, to the best of the authors’ knowledge, there are no current studies suggesting that providing participants with information about diet and nutrition has any direct effect on sleep duration, or on young adults’ driving behaviour. This program will be identical to the active intervention with respect to exposure (time-matched) and format (4 purpose built educational video vignettes), but the sleep-related information will be replaced with diet and nutrition related content. For example, participants in the diet and nutrition group engaged with will be required to engage with 4 × 10 min 'Nutrition Facts' online education modules delivering content covering, a) the fundamentals of diet and nutrition b) the benefits of a healthy diet for performance; c) the benefits (and consequences) of healthy/poor diet and nutrition and d) PIECES: Strategies for healthy eating (Plan, Include fruit and vegetables, Eat with other people; not the TV or that assignment, Choose smaller portions, Experiment, Skip sugary drinks), practical tips for maintaining a healthy diet. No pledge of behaviour change will be signed by the Placebo group. Furthermore, participants in the diet and nutrition education group will not receive education or instruction specifically about their sleep, nor any sleep-related feedback during the intervention phase.

#### Outcome measures

2.1.1

Objective driving and sleep measures will be used in the trial to directly address the primary and initial secondary research objectives.

### Primary outcome 1: risky driving performance

2.2

On-road risky driving performance will be assessed using small, sensitive, 3-axis accelerometers (GeneActiv Original, ActivInsights). The accelerometer is placed in a zip lock bag on a flat surface in the boot/trunk of the participant's vehicle and secured with duct tape. The device is oriented so that: x captures forwards-backwards acceleration, y captures left-right acceleration, and z captures up-down acceleration. These devices objectively record vehicular forces of acceleration from discrete vehicle events in forward and lateral directions, e.g., overcorrection after attentional drifts when drowsy [43] and provide an ecologically meaningful assessment of driving performance [44]. Previous research suggests that elevated g-force events have high predictive accuracy for crash and near-future crashes in young adults [43], and therefore provide a proxy measure of risky driving in young drivers [45].

Risky driving indices (elevated g-force events) extracted from these devices for analysis will include;−Rapid starts (throttle acceleration): defined as forward acceleration (m/s^2^),−Hard stops: defined as longitudinal acceleration due to braking (m/s^2^),−Hard left turns: defined as lateral acceleration to the left side (m/s^2^), and−Hard right turns: defined as lateral acceleration to the right side (m/s^2^).

Extending on prior research [43], a custom composite ‘risky driving variable’ will be created from these g-force indices and taking into consideration each participant's driving data per day and aggregated across the week, and at times of increased driving risk (e.g., driving at night/in the morning and at the circadian nadir). Changes in the risky driving composite from baseline to post-intervention will be used in primary analyses.

To minimise the risk of use by other drivers, participants will 1) be included in the study if they own their own private vehicle, 2) be asked to refrain from lending their vehicle to others during the study periods, and 3) complete a driving diary. Further, validation between wrist and car actigraphy is planned in secondary analyses of the study.

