#### Sample size

1.1.2

A minimum sample size of 189 participants was initially calculated. We will aim to recruit 210 participants, allowing for ∼10% attrition at follow-up (consistent with drop-out from our previous studies in this age cohort). Based on the authors’ previous studies using the same measurement approach (h^2^_p_ = 0.12–0.37) [38], this sample size will provide 90% power, with a significance level of *p* = 0.05, to detect a 'small’ change in the primary driving outcome based on a parallel groups design with 0.3 correlation among the repeated measures. In addition, this sample size will provide 90% power to detect a 'small-medium effect size’ of a 5% increase in mean objective sleep duration (primary sleep outcome - equivalent to approximately 25 min additional sleep per night). This is a clinically and physiologically significant change [39], representing almost three extra hours of sleep each week. Based on our previous laboratory work [38] the study is also sufficiently powered for all proposed secondary outcomes.

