## Analyses

3

Analyses of change in the primary and secondary outcomes will be conducted on an intention-to-treat (ITT) basis using all randomised participants. The changes in the primary and secondary outcomes will be tested using general linear mixed effects regression models with repeated measures (MMRM; MIXED Procedure in SPSS 22 and STATA 15). These models will include the random intercept for each individual participant and fixed effects for condition (intervention [sleep] vs placebo [nutrition]) and assessment period (baseline, intervention, and 6-month follow-up). Where appropriate, adjustments for demographic variables will be made via their inclusion as additional fixed effects. The outputs of analyses will be reported via significance (as confidence intervals) and magnitude estimates to guide clinical interpretation.

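### The primary driving outcome is analysed as unadjusted change from baseline; at the plan's own correlation of 0.3 this is 35% less efficient than adjusting for baseline, and less precise than ignoring it

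*Protocol article*

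**What the plan says.** Section 2.2 of the protocol article defines the composite driving outcome and fixes how it enters the primary analysis: "Changes in the risky driving composite from baseline to post-intervention will be used in primary analyses".

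Section 3 (Analyses) names the method as "general linear mixed effects regression models with repeated measures (MMRM; MIXED Procedure in SPSS 22 and STATA 15"). It specifies the model as follows: "These models will include the random intercept for each individual participant and fixed effects for condition" and for "assessment period (baseline, intervention, and 6-month follow-up"). Baseline is therefore one of the repeated outcomes. The only covariates mentioned are demographic: where appropriate, "adjustments for demographic variables will be made via their inclusion as additional fixed effects". The baseline value of the outcome is not named as a covariate, equal baseline means are not imposed, and no residual covariance structure is given beyond the random intercept.

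Section 1.1.2 (Sample size) powers the driving outcome on a "parallel groups design with 0.3 correlation among the repeated measures", with 90% power at the 0.05 level and a minimum of 189 participants. The target change is described only as small, without a number. Section 2.3 puts the three assessment periods at weeks 1–2, 7–8 and 33–34.

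**The concern.** A change score subtracts the whole baseline value. That helps when baseline and outcome are strongly correlated. When the correlation is below 0.5, subtraction adds more noise than it removes, and the comparison becomes less precise than one that never used baseline. The plan's own value of 0.3 lies in that range.

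At stake is the precision of the primary driving comparison, in a trial that aims to detect a small change. The loss can be avoided because baseline is already measured on everyone. Section 1.1.3.1 also says participants do not learn their allocation until their baseline laboratory assessments are complete, so equal expected baseline means are a safe assumption.

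The covariance raises a smaller concern. A random intercept with independent residuals gives every pair of periods the same correlation, although the periods are very unevenly spaced.

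**Working it through.** **Inputs.** From Section 1.1.2: ρ = 0.3, N = 189, attrition about 10%, power 90%, significance level 0.05. From Section 2.3: weeks 1–2, 7–8 and 33–34. Assumed: 1:1 allocation, a two-sided test, the same SD at each period, complete data.

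**The plan's own figures.** 189/(1 − 0.10) = 210, so the recruitment target reproduces. The 189 itself cannot be rebuilt, because the driving effect has no numeric value. If small is taken as f = 0.10 (an assumption), a group-by-time test at ρ = 0.3 needs 370 participants with two periods or 297 with three. Values near f = 0.14 (two periods, 190) or f = 0.125 (three periods, 191) come close to 189.

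**Variance factors.** In units of SD², with the variance of the treatment contrast equal to factor × 4/N:

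| Analysis | Factor | At ρ = 0.3 |
|---|---|---|
| Change from baseline (free baseline mean per arm) | 2(1 − ρ) | 1.40 |
| Post-intervention value, baseline ignored | 1 | 1.00 |
| Baseline adjusted or baseline means constrained | 1 − ρ² | 0.91 |

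Generalised least squares on a three-period equal-correlation covariance gave 1.40 for the random-intercept model with condition-by-period effects and 0.91 with a common baseline mean, which agrees with the formulas.

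**Loss relative to adjustment.** 1 − (1 − ρ²)/[2(1 − ρ)] = 1 − (1 + ρ)/2 = (1 − ρ)/2.

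| ρ | Change | Adjusted | Loss |
|---|---|---|---|
| 0.1 | 1.80 | 0.99 | 45% |
| 0.3 | 1.40 | 0.91 | 35% |
| 0.5 | 1.00 | 0.75 | 25% |
| 0.7 | 0.60 | 0.51 | 15% |

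**Consequence at N = 189, ρ = 0.3.** The effect detectable with 90% power is 3.2415 × SE.

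- Change: SE = √(1.40 × 4/189) = 0.172; detectable effect 0.558 SD.
- Baseline ignored: SE = √(4/189) = 0.145; detectable effect 0.472 SD.
- Baseline adjusted: SE = √(0.91 × 4/189) = 0.139; detectable effect 0.450 SD.

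An effect of 0.450 SD, which the adjusted analysis detects with 90% power, has about 74% power by change. Reaching 90% by change would take 189 × 1.40/0.91 ≈ 291 participants (292 for equal arms).

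**Covariance.** The gaps between corresponding weeks are 7 − 1 = 6, 33 − 7 = 26 and 33 − 1 = 32 weeks. As an illustration only, assume correlations of 0.4 (baseline–post), 0.3 (post–follow-up) and 0.2 (baseline–follow-up). Their mean is 0.3, so an equal-correlation model uses 2(1 − 0.3) = 1.40 for both changes. The true values are 2(1 − 0.4) = 1.20 and 2(1 − 0.2) = 1.60. The model SE is then √(1.40/1.20) = 1.08 times the true one for baseline to post (8% too large), and √(1.40/1.60) = 0.935 times for baseline to follow-up (6.5% too small). Under this illustration the baseline–post correlation is 0.4, so the loss from using change would be (1 − 0.4)/2 = 30%. The 8% and the 35% therefore belong to different assumptions and should not be added together.

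**The case against.** **The criticised model is not quite the one written.** Section 3 lists condition and period but no condition-by-period term. Read literally, the condition effect is an average over all three periods, baseline included, with factor (1 + 2 × 0.3)/3 = 0.53, and no difference in change is estimated. This stands as a condition on the 1.40: it applies once the interaction is added. Section 2.2 and the opening of Section 3 both require a test of change, so some such term is needed.

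**Change can be analysed with baseline as a covariate**, which gives the same treatment effect as adjusting the post value, and a fuller analysis plan may do this. That is possible. However, the text sets out a model whose named covariates are demographic only, so the reader is given an analysis without baseline adjustment.

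**The size depends on ρ.** This stands. The 0.3 is a planning value, and the loss shrinks as the correlation rises.

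**The stated 90% power.** A reader might infer that the sample size claim is wrong. The document does not support that: a group-by-time calculation already contains (1 − ρ), and the 189 cannot be checked without a numeric effect. The 0.56 and 0.45 SD compare two analyses; they do not test the plan's claim.

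**Bias and type I error.** A reader might also infer a biased estimate, or a primary test that rejects too often. Neither follows. Change is unbiased under randomisation, and if correlation decays with time the SE error on baseline to post is conservative. Nor does the text force equal correlation, since the MMRM label may stand for a residual structure stated elsewhere. What remains is that the label and the only covariance term given need to be reconciled.

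**Conclusion.** The point holds as an avoidable loss of efficiency on the primary driving comparison. At the plan's own correlation of 0.3, unadjusted change gives up 35% of the information that baseline adjustment would retain, and it is less precise than not using baseline at all (1.40 against 1.00). The second statement holds for any ρ below 0.5; at 0.5 the two are equal. Some loss relative to adjustment remains at every ρ below 1.

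This rests on a condition-by-period term being added, equal SDs across periods, 1:1 allocation and no baseline adjustment specified elsewhere.

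The covariance point is secondary. Its direction is clear if correlation decays with time: the SE is too large for baseline to post and too small for baseline to follow-up. Its size depends wholly on correlations the document does not give.

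**What to change.** In Sections 2.2 and 3, replace the unadjusted change analysis with one of the following:

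- A constrained longitudinal model: all three periods as outcomes, one common baseline mean for both arms, separate condition effects at the intervention and follow-up periods, and an unstructured covariance in place of the random intercept. The primary estimate is the condition effect at the intervention period.
- A mixed model on the two post-baseline periods, with baseline and baseline-by-period as covariates, condition-by-period effects and an unstructured covariance.

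Either choice supplies the missing interaction and makes the MMRM label accurate. The first also keeps participants who have only some of the three periods, in line with the intention-to-treat statement in Section 3.

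The cost is wording, settled before outcome data are examined by arm. No extra data or visits are needed. An unstructured three-period covariance has six parameters, against two for a random intercept with independent residuals, which about 189 participants support easily.

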### Initial secondary outcome: objective sleep

2.3

Objective assessment of sleep-wake states will be determined using wrist-worn accelerometers (i.e. actigraphs). Using specific scoring algorithms, actigraphy can provide a non-invasive and objective method of measuring habitual sleep and activity levels in naturalistic settings [41], and is comparable to polysomnography as a valid and reliable measure of sleep-wake parameters, particularly for sleep onset and wake times [42]. The GeneActiv Original actigraphs are wrist-watch style accelerometers that record raw triaxial linear accelerometry signals (movement) and ambient light (Lux) onto on-board memory.

Actigraphy data will be recorded over two weeks at each measurement point: Baseline Driving Assessment (Weeks 1 and 2), Post-intervention Driving Assessment 2 (Weeks 7 and 8), and during Follow-up Driving Assessment (Weeks 33 and 34).

The following sleep outcomes will be extracted from the actigraphy data;-Habitual daily sleep duration (minutes of sleep obtained across each 24-h period during data collection)-Frequency of sleep restriction (frequency count of sleep duration < 6 h s per night each week)

A further extensive list of sleep outcomes are also planned, however, this is the planned initial analysis.

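### Nights under 6 h are analysed as a raw weekly count with no valid-night denominator, so missing actigraphy nights bias the arm contrast if wear differs and shrink it if wear is equal

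*Protocol article*

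**What the plan says.** Protocol article, section 2.3 (Initial secondary outcome: objective sleep), lists two actigraphy outcomes for the first planned analysis. One is habitual sleep duration. The other is sleep restriction, defined as a "frequency count of sleep duration < 6 h s per night each week". The definition has a threshold and a time unit but no denominator. The same section says that "Actigraphy data will be recorded over two weeks at each measurement point", which gives up to 14 nights per assessment period.

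Section 3 (Analyses) covers all outcomes, primary and secondary alike, and says that change in them "will be tested using general linear mixed effects regression models with repeated measures (MMRM; MIXED Procedure in SPSS 22 and STATA 15". The named terms are a random intercept per participant and fixed effects for condition and assessment period. Covariates are limited to demographics: "Where appropriate, adjustments for demographic variables will be made via their inclusion as additional fixed effects". No term carries the number of nights observed, and no count or binomial model is offered.

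The outcome matters to the trial's argument: fewer nights below 6 h is the second hypothesis in section 1.1.1.

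**The concern.** The outcome is a count bounded by the number of nights on which the device gave usable data. A participant who is short of sleep on the same share of nights as before, but whose record loses two nights, scores lower. The mixed model does not repair this. It can accommodate an assessment period that is missing altogether, but a night lost within an observed period has already lowered the score before any model is fitted.

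Two consequences follow. If the arms lose different numbers of nights, the difference in wear enters the treatment contrast as if it were a difference in sleep. The direction depends on which arm loses more. If the arms lose the same number, there is no false difference, but a real one is understated.

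Different wear is possible because only the sleep arm gets a prescribed schedule and signs a pledge (sections 2 and 2.1). The documents give no evidence on whether it will happen or in which direction. Section 1.1.3.1 relies on objective outcome measures to limit ascertainment bias, and a score that depends on wear weakens that protection.

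**Working it through.** **The plan's own figures.** The article gives no figure for valid nights or for the variance of this outcome. The related figure that can be checked is the recruitment target in section 1.1.2: 189 / (1 - 0.10) = 210, which reproduces. Half of 189 is 94.5, so 94 per arm is used below.

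**Inputs from the article.** Up to 14 nights per period (section 2.3). At least 2 short nights in 7 for eligibility, self-reported (Table 1), so a nightly probability of 2/7 = 0.286 is a natural lower case. 3/7 = 0.429 is added as a higher case.

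**Assumptions.** Valid nights per week in each arm after baseline; a complete baseline; a between-person SD of 0.8 on the logit scale; nights lost independently of how long the person slept; two-sided 5% level.

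**Expected count.** With nightly probability p and V valid nights per week, the expected raw count is p x V.

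- One participant with 5 of 7 valid nights: 1 - 5/7 = 28.6% below the full-week expectation.
- Equal wear V in both arms, with a true difference in p: the contrast is V x (p_control - p_sleep). At V = 5 it is 5/7 of the full-week value, so 28.6% smaller.
- Unequal wear and the same p: the contrast (sleep minus control) is p x (V_sleep - V_control). At p = 2/7 and 5.5 versus 6.5 nights this is 0.286 x (-1.0) = -0.29 nights per week. The simulated value is slightly larger (-0.31), because spreading individuals on the logit scale raises the average probability a little above 2/7.

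**Simulation under no true effect.** 94 per arm, 4,000 replicates, test on change from baseline. The raw weekly count is compared with 7 x (short nights / valid nights).

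| p | Valid nights per week, sleep v control | Raw count: difference per week | Raw count: rejections | Proportion x 7: rejections |
|---|---|---|---|---|
| 2/7 | 6.9 v 6.9 | 0.00 | 5.0% | 5.1% |
| 2/7 | 6.0 v 6.0 | 0.00 | 5.4% | 5.5% |
| 2/7 | 5.0 v 5.0 | 0.00 | 5.1% | 5.6% |
| 2/7 | 6.5 v 6.0 | +0.15 | 15.3% | 5.7% |
| 2/7 | 6.0 v 6.5 | -0.15 | 15.7% | 5.1% |
| 2/7 | 5.5 v 6.5 | -0.31 | 45.5% | 5.3% |
| 2/7 | 5.0 v 6.5 | -0.47 | 79.8% | 5.3% |
| 3/7 | 6.0 v 6.5 | -0.22 | 23.3% | 5.1% |
| 3/7 | 5.5 v 6.5 | -0.44 | 67.7% | 5.4% |
| 3/7 | 5.0 v 6.5 | -0.66 | 95.1% | 5.6% |

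With equal wear the raw count holds its error rate. With unequal wear it does not, and dividing by valid nights restores it: 5.0% to 5.7% in every scenario run. The row with more loss in the control arm (6.5 v 6.0) shows the bias reversing sign.

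**The case against.** The strongest reply is that minimum wear, valid-night rules and scaling to a 7-night week are ordinary analysis-plan content. A weekly figure from a two-week recording already needs some averaging rule, and a condensed article need not print it. That is fair, and the absence of a wear rule is not the point here. The point rests on what the article does state: a count as the outcome, and a linear model with a named set of terms. A wear rule elsewhere would limit the harm. Unless it required every night or rescaled the count, the score would still fall with each lost night.

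It is also fair that both arms wear the same device over the same windows, and that nothing in the article predicts unequal wear. A reader might infer that missing nights will always look like benefit. They will not: that needs greater loss in the sleep arm.

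A reader might also treat the Gaussian model for a bounded count as the main fault. The simulation does not support this. With about 94 per arm and equal wear, the linear test on change kept close to 5% error. The denominator matters more than the distribution.

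Finally, a reader might extend the point to the primary driving outcome and say that event totals are analysed without regard to time driven. The article does not fix that. Section 2.2 calls the indices events but defines them on an acceleration scale, for example "Rapid starts (throttle acceleration): defined as forward acceleration (m/s^2". The variable analysed is a custom composite whose formula is not given and which considers "driving data per day and aggregated across the week, and at times of increased driving risk". That wording could include normalisation for exposure. The earlier bedtime in the section 2 example is not evidence that anyone drives less.

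**Conclusion.** The point holds for the short-sleep outcome. As written, the count depends on wear as well as sleep, and the analysis has no term to separate the two. Equal loss shrinks a true difference in proportion to the nights lost (29% at 5 of 7). Unequal loss biases the contrast by roughly the nightly probability times the gap in valid nights. A gap of one night per week (5.5 v 6.5) gives about -0.3 nights per week and a false-positive rate near 46% at p = 2/7, or about -0.4 and 68% at p = 3/7. A half-night gap gives 16% and 23%.

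These sizes rest on assumed wear, an assumed between-person SD, nights lost independently of sleep length, and a change-score test standing in for the full mixed model. They show sensitivity to wear and do not predict what the trial will see. No size can be given for driving, and no claim is made there. This is a definition worth correcting before analysis in an outcome that tests a stated hypothesis. It is not a flaw in the trial's design.

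**What to change.** Redefine the outcome as short nights out of valid nights. Analyse it with a binomial (logit) mixed model: numerator, nights under 6 h; denominator, valid actigraphy nights in the period; the planned participant random intercept; and condition, assessment period and their interaction, which carries the treatment contrast. Report valid nights per week by arm and period alongside the result, so that readers can see whether wear differed.

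The cost is a change of wording and of model call. Valid nights come from the actigraphy already collected. There are two limits. The effect is an odds ratio, so it should be converted back to nights per week for interpretation. The denominator also corrects only for how many nights are missing: if nights are lost because of how the person slept, the proportion can still be biased, which is a further reason to report wear by arm.
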